### Statistical analysis

Data will be analysed using RStudio version 1.2.13 software (RStudio, Massachusetts, United States). For continuous variables, results will be expressed as mean and standard deviation. Data distribution will be tested for normality using a Shapiro-Wilk test. If the variables are not normally distributed, the following statistical tests will be used: for dichotomous variables, a chi-square test will be used to determine difference between groups; while, for continuous variables, a Kruskal-Wallis test will be used for between-group comparison. If expression levels of biomarkers are below the detection limit, they will be replaced by the value 0 for analysis purposes. A p-value of <0.05 is considered significant.

For objective 1 the expression of each cytokine will be expressed as mean and standard deviation for participants from each MACRO trial arm. For objective 2 each MACRO trial arm will be analysed separately. Logistic regression analysis will be performed to determine the impact of cytokine expression levels on binary responder status (defined as a minimum 10-point improvement in baselines SNOT-22 score at 6 months). For objective 3 logistic regression analysis will be performed to determine the impact of cytokine expression levels on phenotypic characteristics such as the presence of nasal polyps or raised total serum IgE (>100 IU/ml). For objective 4 microbiome profiles will be reported as mean distribution of bacterial strains. Bacterial profiles will be compared alongside outcomes from the MACRO trial database using univariate and multivariate statistics, associating microbiome profiles to cytokine profiles and treatment success on included patients.

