**Methods:**

Adult CRS patients enrolled into the MACRO trial will be recruited from participating UK otorhinolaryngology departments. Nasal tissue samples and swabs will be obtained in theatre or clinic from patients randomised to all three trial arms. Nasal tissue will be analysed with multiplex electrochemiluminescence for 32 cytokines including IL-5, IL-13, IgE and periostin. Bacterial swabs will be analysed using illumina miSeq 16S amplicon sequencing. Mean expression for each biomarker will be reported for treatment responder and non-responder groups. Correlation of biomarkers with MACRO trial outcome data such as endoscopic evaluation scores and quality-of-life improvement scores will be reported.

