## Methods

### Objectives

The ExpRess study is a multicentre prospective cohort study of adult patients with CRS recruited from at least five UK hospitals in parallel to the MACRO randomised controlled trial. Recruitment is currently ongoing at James Paget University Hospital, Norfolk and Norwich University Hospital, Guy’s and St Thomas’ NHS Foundation Trust, Imperial College Healthcare NHS Trust and Newcastle upon Tyne Hospitals NHS Foundation Trust. Study objectives include:

To quantify the cytokine expression pattern for MACRO trial participants,To determine if cytokine expression varies between treatment responder and non-responder groups,To identify if phenotypic characteristics collected from MACRO patients can be predicted by cytokine profiles,To define the bacterial profiles of MACRO trial participants.

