### Recruitment

Participants will be recruited from January 2019 to September 2023 from participating UK sites. The recruitment target will be 120 patients in total across all three arms of the MACRO trial; equating to approximately 40 participants per arm. An a-priori sample size calculation was not possible due to lack of information around the baseline prevalence and variance of each cytokine included within the study groups and the likely difference between groups.

Patients will be approached for recruitment to ExpRess following randomisation to any of the three MACRO trial arms of surgery, macrolide antibiotics or placebo. Patients will be approached in clinic by the principal investigator or the research nurse and will be given a recruitment pack that will include a participant information sheet (S1 File) and consent forms. Following written informed consent, patients will have nasal tissue samples and endoscopically guided nasal swabs collected either at the point of randomisation or at their 6 month follow up visit. Participants randomised to the surgical arm of the MACRO trial are also eligible to have samples collected at the time of surgery instead, which is within 6 weeks of randomisation. This process is outlined in Fig 1.

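### Objective 3 analyses total serum IgE only as above or below 100 IU/ml; a full-scale analysis would usually have more power, by an amount the document cannot fix

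*Protocol article*

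**What the plan says.** The Objectives section of the protocol article states the third aim: "To identify if phenotypic characteristics collected from MACRO patients can be predicted by cytokine profiles". The Statistical analysis section gives the method: "For objective 3 logistic regression analysis will be performed to determine the impact of cytokine expression levels on phenotypic characteristics". It names two example phenotypes: "phenotypic characteristics such as the presence of nasal polyps or raised total serum IgE (>100 IU/ml"). Significance is set per test: "A p-value of <0.05 is considered significant". No continuous analysis of serum IgE is described.

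On size, the Recruitment section says: "The recruitment target will be 120 patients in total across all three arms of the MACRO trial". It adds: "An a-priori sample size calculation was not possible due to lack of information around the baseline prevalence and variance of each cytokine". The separate analysis of each arm is stated for objective 2 only, so objective 3 is read here as using all participants together.

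**The concern.** Polyp presence is naturally yes or no. Serum IgE is not: a value in IU/ml must exist before the cut can be applied. Under the cut, a participant at 101 IU/ml counts the same as one at 2000 and the opposite of one at 99. If cytokine level rises or falls smoothly with IgE, that information is thrown away.

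At stake is whether objective 3 can detect a real association between a cytokine and IgE. The sample is modest and was not sized for this question. A null result for IgE could then come from the cut as easily as from the biology.

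**Working it through.** **Plan's own figure.** The article states no power or effect size, so there is none to reproduce. Its only sample-size arithmetic agrees: 120 / 3 = 40 per arm.

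**Inputs from the article.** n = 120 (Recruitment); significance level 0.05 (Statistical analysis; two-sided assumed); one cytokine per model (assumed).

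**Assumptions, not in the article.** Correlation r between cytokine and log serum IgE of 0.10 to 0.40; share p above 100 IU/ml of 20% to 50%; both variables normal on the scale analysed; a serum value for every participant.

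**Step 1: full scale.** By the Fisher z approximation, power = Φ(atanh(r) × √(n − 3) − 1.96), where √117 = 10.817. The opposite tail is negligible except at the smallest r.

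**Step 2: after the cut.** The correlation shrinks to r × φ(z_p) / √(p(1 − p)). The factor is 0.798 at p = 50%, 0.789 at 40%, 0.759 at 30% and 0.700 at 20%.

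**Step 3: one case in full, r = 0.25 and p = 30%.**
- Full scale: atanh(0.25) = 0.2554; 0.2554 × 10.817 = 2.763; 2.763 − 1.96 = 0.803; power 78.9%.
- Cut: 0.25 × 0.759 = 0.190; atanh = 0.192; 0.192 × 10.817 = 2.078; 2.078 − 1.96 = 0.118; power 54.7%.
- Loss: 78.9 − 54.7 = 24.2 points.

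**Step 4: the range.** Loss in power, in percentage points:

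| r | Full-scale power | p = 50% | p = 40% | p = 30% | p = 20% |
|---|---|---|---|---|---|
| 0.10 | 19.2% | 5.3 | 5.5 | 6.2 | 7.4 |
| 0.15 | 37.3% | 11.7 | 12.2 | 13.7 | 16.6 |
| 0.20 | 59.2% | 17.9 | 18.7 | 21.2 | 26.0 |
| 0.25 | 78.9% | 19.9 | 20.9 | 24.2 | 30.8 |
| 0.30 | 91.7% | 16.6 | 17.6 | 21.0 | 28.2 |
| 0.35 | 97.7% | 10.3 | 11.1 | 14.0 | 20.5 |
| 0.40 | 99.6% | 4.9 | 5.4 | 7.2 | 12.0 |

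**Step 5: simulation check.** This compared a linear test with the logistic likelihood-ratio test at n = 120. For r of about 0.20 to 0.30 and p of 30% to 50%, the loss was about 15 to 24 points, in line with the formula. In the mildest corner (r = 0.40, p = 50%) it was about 4 points.

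**Step 6: sample-size equivalent.** For modest correlations, information is kept in proportion to the squared factor. At p = 50% this is 120 × 2/π = 76 participants; at p = 30%, about 69.

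**Step 7: sensitivity to shape** (simulation, r = 0.20 to 0.30, p = 30% or 50%).
- Cytokine entered raw, with lognormal skew: the loss is about 8 to 22 points at a log-SD of 1.0 and about 1 to 15 points at a log-SD of 1.5.
- Cytokine level steps by 0.4 to 0.6 SD exactly at the cut: the logistic model has about 53% to 90% power and the linear model about 33% to 72%. The direction reverses.

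**The case against.** The strongest reply is that the size, and even the sign, of the effect rests on a shape the article does not give. Bivariate normality favours the linear test by construction. The plan states no log transform of cytokines and sets values below the detection limit to 0, where a log is undefined, so the predictor may well be skewed. If raised IgE marks a distinct class, the logistic model is the better test. This stands as a limit on the figure. It does not remove the point: nothing in the article suggests that cytokine levels jump at 100 IU/ml, and a full-scale model was the more powerful one under smooth association over r = 0.20 to 0.30, though by very little under heavy skew.

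A reader might infer that the plan excludes every continuous analysis of IgE. The text does not support that. IgE is introduced as an example, and the fuller documents are not shown. What can be said is that the article fixes this variable, this cut and this model, and describes no other analysis. For the same reason, the lack of a stated rationale for 100 IU/ml is not a fault. The threshold is set in advance, so it is not data-driven either.

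Two further limits stand. A ratio of IgE levels answers a somewhat different question from the odds of raised IgE. And the Outcome measures section does not name serum IgE among the MACRO data, while the IgE in the Laboratory analysis section is measured in tissue. The numeric serum value may therefore be missing for some or all participants.

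**Conclusion.** The point holds as a conditional loss of power and a cheap improvement. With 120 participants, a correlation of 0.20 to 0.30 on normal (log) scales and 30% to 50% above the cut, power falls by about 15 to 24 points. Over 0.10 to 0.40 and 20% to 50% it falls by about 5 to 31 points. It would be tempting to state 15 to 24 points per cytokine as a property of this study. The article does not support that: it gives neither input and says such information was lacking, and the 0.20 to 0.30 range lies near where the loss peaks.

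The weight is moderate. One example phenotype within objective 3 is affected. The primary outcome, based on SNOT-22 responder status, and the polyp analysis are untouched.

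**What to change.** In the Statistical analysis section, under objective 3, state that where the numeric serum IgE value is available in the linked MACRO data, the main IgE analysis is a linear regression of log total serum IgE on cytokine level. Report the ratio of IgE per unit or per SD of cytokine with its 95% CI, and state the scale on which cytokines enter. Keep the logistic model at 100 IU/ml as a secondary analysis, and leave polyp presence as logistic. First confirm that the recorded value, and not only the flag, will be linked, and for how many participants.

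The cost is one sentence and one extra model per biomarker, with no new samples, visits or participants. Linkage follows completion of MACRO, so the change can be fixed before linked results are seen. The downsides are that the main result becomes a ratio of IgE levels and not an odds ratio for raised IgE, and that the linear model would be the weaker test if the association were truly a step at 100 IU/ml. The retained logistic model covers both.

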## Discussion

Defining clear endotypes in CRS will help to refine patient pathways for the efficient use of medical and surgical resources. This work may lay the groundwork for future studies to predict which patients might respond to medical or surgical therapy. Patients undergoing surgery for CRS in the UK can have treatment costs totalling >£2,000 per year, compared to macrolide antibiotics prescriptions costing <£10/year [9]. In a retrospective study of 88,317 patient with CRS, 46% were prescribed antibiotics for CRS and 26% had more than 10 recorded prescriptions during follow up, suggesting that CRS is a significant target for antibiotic stewardship [10]. Better understanding of the CRS microbiome and biomarker profiles will help to rationalise these prescriptions in primary care and contribute to targeting the global threat of antimicrobial resistance.

The strengths of this study include a large sample size and multicentre approach to recruitment to ensure a diversity of CRS phenotypes is captured. Limitations include the restriction of cytokine targets due to resources available within our institution. However, the most important cytokine targets such as IL-5, IL-13 and periostin have been identified through a thorough literature search by our team and are including within our analysis. An additional limitation is the lack of microbiome data for patients recruited to ExpRess prior to November 2022. Due to a lack of data on the baseline values and variance of all cytokines and microbiome profiles within the study population, formal sample size calculations were not possible. We will therefore liaise closely with recruiting centres and aim to extend the study to other sites to ensure adequate patient numbers for microbiome analysis are achieved.

Any study amendments will be submitted to the Integrated Research Application System for subsequent management by the Research Ethics Committee. Amendments will require approval by the study team and all study documents will be kept updated appropriately. We would aim to publish the results of this study in peer reviewed journals and present nationally and internationally at relevant meetings. Lay summaries for patients and the public will be produced and disseminated through the MACRO trial and University of East Anglia Rhinology and ENT Research Group websites.

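### Objective 4 links microbiome profiles to treatment success without fixing how trial arm or swab timing is handled, and promises strains from a 16S assay

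*Protocol article*

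**What the plan says.** The Statistical analysis section of the protocol article says: "For objective 4 microbiome profiles will be reported as mean distribution of bacterial strains". It adds that profiles will be set against MACRO outcomes by univariate and multivariate methods, "associating microbiome profiles to cytokine profiles and treatment success on included patients". The same section reports objective 1 by trial arm and analyses objective 2 separately within each arm. For objective 4 it states neither an arm rule nor a timing rule.

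Four other places bear on this:

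- **Recruitment:** tissue and swabs are collected at randomisation or at the 6-month visit. Surgical-arm participants may instead be sampled at surgery, within 6 weeks of randomisation.
- **Introduction:** one arm receives clarithromycin for 2 weeks and then a further 10 weeks at a lower frequency.
- **Outcome measures:** a responder has improved by at least 10 SNOT-22 points from baseline at 6 months.
- **Abstract, Methods:** "Bacterial swabs will be analysed using illumina miSeq 16S amplicon sequencing".

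On numbers, Recruitment says: "The recruitment target will be 120 patients in total across all three arms of the MACRO trial", which it describes as "equating to approximately 40 participants per arm". The Discussion says: "An additional limitation is the lack of microbiome data for patients recruited to ExpRess prior to November 2022". It adds that no sample size calculation was possible and that further sites will be sought so that microbiome numbers are adequate. No expected number of swabs is given.

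**The concern.** A link between bacteria and treatment success is useful for selecting patients only if the bacteria were measured before treatment could change them. Here some swabs come before the allocated treatment and some after it, and one of the treatments is an antibiotic. If both kinds enter one analysis of response, the effect of treatment on the bacteria is mixed with any predictive value the bacteria have. The resulting association could be read as a microbial endotype of responders when it reflects which arm a participant was in, or the fact that the nose had already improved.

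A separate problem is that the promised reporting unit, strains, is finer than the named assay generally delivers. A third is that a reader planning follow-on work cannot tell from the article how many participants objective 4 will rest on.

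**Working it through.** **1. Timing of a 6-month swab.** The scheduled clarithromycin course is 2 + 10 = 12 weeks. Six months is about 26 weeks, so if the course starts at randomisation, a 6-month swab falls about 26 − 12 = 14 weeks after its scheduled end. It also coincides with the SNOT-22 assessment that classifies the participant as responder or non-responder. Such a swab cannot serve as a baseline predictor. The article does not say how much antibiotic effect would remain after that interval, so the effect is possible rather than established.

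**2. How arm can create an association.** Suppose that within each arm a taxon has no relation to response. Suppose also that a fraction f of macrolide-arm swabs are 6-month swabs, that the course shifts the taxon's mean by δ in those swabs, and that timing is unrelated to response. If arm and timing are ignored, the expected difference between responders and non-responders is

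D = f × δ × [P(macrolide arm | responder) − P(macrolide arm | non-responder)].

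D is zero only if f = 0, δ = 0, or the macrolide arm has the same response rate as the other arms combined. The same argument applies to 6-month swabs taken after surgery. The article gives no values for f, δ or the response rates, so D cannot be given a number.

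**3. Why an arm rule alone is not enough.** Even within one arm, a 6-month swab and the 6-month SNOT-22 score describe the same moment. Improvement may have changed the bacteria, rather than the bacteria having predicted improvement. Sampling time therefore needs its own rule.

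**4. Reporting unit.** The Abstract names a 16S amplicon assay and the Statistical analysis section promises strains. As a general methods point, not taken from the article, short-read 16S data generally resolve to genus and sometimes to species.

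**5. Number of participants with swabs.** The only stated figure is 120 for the whole study, and 120/3 = 40 per arm agrees with the article. The swab number has to be inferred from the dates:

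- Recruitment window, January 2019 to September 2023 inclusive: 4 × 12 + 9 = 57 months.
- Window with swabs, November 2022 to September 2023 inclusive: 2 + 9 = 11 months.
- Even accrual to exactly 120 (assumption): 120 × 11/57 = 23.2, or 23.2/3 = 7.7 per arm. Counting days gives 120 × 334/1,734 = 23.1.
- If the share recruited from November 2022 onwards were 10%, 30%, 40% or 50% (assumed): 12, 36, 48 or 60 participants.

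**6. What such numbers can detect.** For one taxon, two-sided alpha 0.05 and 80% power, the detectable standardised difference is (1.960 + 0.842) × √(1/n₁ + 1/n₂). The responder split is assumed, because the article gives none.

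| Participants with swabs | Detectable difference, 50:50 split | Detectable difference, 70:30 split |
|---|---|---|
| 12 | 1.62 SD | 1.76 SD |
| 23 | 1.17 SD | 1.27 SD |
| 48 | 0.81 SD | 0.88 SD |
| 60 | 0.72 SD | 0.79 SD |

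These figures come before any split by arm or sampling time and before any correction for multiple taxa. With 20 independent taxa (assumed) each tested at 0.05, the chance of at least one false positive is 1 − 0.95²⁰ = 0.64.

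**The case against.** Several points on the other side are fair. The article nowhere says that arms or time points will be pooled for objective 4. A reader might infer pooling from the contrast with objective 2, but the text is silent, and multivariate methods could include terms for arm and timing. Such terms are often left to a fuller plan. What stands is narrower: the article commits to an association with treatment success, fixes arm handling for the first two objectives, and leaves both arm and timing open where an antibiotic arm and post-treatment swabs make them matter most.

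A reader might also infer that objective 4 rests on 23 participants and cannot support any association with response. The documents do not support that. The figure of 23 is a calculation under even accrual. The Discussion discloses the missing swabs and plans more sites, and a larger subset could detect large differences. Nor is the limitation hidden. Only the expected number is missing.

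The Objectives section frames objective 4 as defining bacterial profiles, which is descriptive. The primary outcome is cytokine expression, and the Discussion presents the work as groundwork for later studies. That limits the damage, but the last sentence of the Statistical analysis section still goes beyond description.

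Finally, replacing the term strains is a small correction of wording. The choice of a particular distance measure or global test for the profiles is a matter of preference and is not part of this point.

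**Conclusion.** The concern holds in this form: objective 4 associates microbiome profiles with treatment success without fixing how arm or sampling time is handled, while the sampling scheme admits swabs taken after a scheduled antibiotic course or after surgery, at the visit that defines response. A treatment effect on bacteria can therefore appear as, or distort, a microbiome-response association. The direction and size of that distortion cannot be derived from the article. They depend on how many swabs are taken at 6 months, how far treatment shifts the bacteria, and how response differs between arms.

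The promised strain-level report does not match the named assay, given the general resolution limit of 16S data.

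The expected number of participants with swabs should be read as about 23 under even accrual to 120, plausibly 12 to 60 depending on late accrual and added sites. Across that range only fairly large single-taxon differences (about 0.7 to 1.8 SD) would be detectable with 80% power before multiplicity. This supports an exploratory label rather than removing the analysis.

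**What to change.** In the Statistical analysis section, for objective 4:

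1. Report profiles by trial arm and sampling time, at genus or ASV level, and replace the reference to strains.
2. Base any association with response on pre-treatment swabs (taken at randomisation, or at surgery in the surgical arm), adjusted for arm. Confirm in the text that swabs taken at randomisation precede the start of the allocated treatment. Arm adjustment is still needed because consent to ExpRess follows allocation and the surgery-time option exists in one arm only.
3. Report 6-month swabs separately, as post-treatment profiles.
4. Label the response associations exploratory and apply false-discovery control to tests of single taxa.

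In the Discussion, beside the limitation on missing swabs, state the expected number of participants with swabs and the accrual assumption behind it.

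The cost is wording and routine analysis code. The Outcome measures section places linkage to MACRO data after completion of that trial, so these rules can be fixed before outcomes are linked. The downside is that fewer swabs enter the response analysis and its conclusion becomes exploratory.
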